## Abstract

**Introduction:**

Unhealthy lifestyle behaviours continue to be highly prevalent, including alcohol consumption, unhealthy diets, insufficient physical activity and smoking. There is a lack of effective interventions which have a large enough reach into the community to improve public health. Additionally, the common co-occurrence of multiple unhealthy behaviours demands investigation of efforts which address more than single behaviours.

**Methods and analysis:**

The effects of six components of a novel digital multiple health behaviour change intervention on alcohol consumption, diet, physical activity and smoking (coprimary outcomes) will be estimated in a factorial randomised trial. The components are designed to facilitate behaviour change, for example, through goal setting or increasing motivation, and are either present or absent depending on allocation (ie, six factors with two levels each). The study population will be those seeking help online, recruited through search engines, social media and lifestyle-related websites. Included will be those who are at least 18 years of age and have at least one unhealthy behaviour. An adaptive design will be used to periodically make decisions to continue or stop recruitment, with simulations suggesting a final sample size between 1500 and 2500 participants. Multilevel regression models will be used to analyse behavioural outcomes collected at 2 months and 4 months postrandomisation.

**Ethics and dissemination:**

Approved by the Swedish Ethical Review Authority on 2021-08-11 (Dnr 2021-02855). Since participation is likely motivated by gaining access to novel support, the main concern is demotivation and opportunity cost if the intervention is found to only exert small effects. Recruitment began on 19 October 2021, with an anticipated recruitment period of 12 months.

**Trial registration number:**

ISRCTN16420548.

Strengths and limitations of this studyPragmatic recruitment of individuals seeking help online to a factorial trial allow for dismantling of the effectiveness of the components which make up a digital multiple health behaviour change intervention.An adaptive trial design reduces the risk of under-recruitment and over-recruitment of participants.Despite double blind procedures, research participation effects may affect self-reported outcomes and introduce bias.Single face-valid items used to measure mediators reduce participant burden but may limit the interpretation of findings.

## Introduction

Behavioural risk factors, such as harmful alcohol consumption, unhealthy diets, insufficient physical activity and smoking, contribute to about one-third of global disability-adjusted life-years, and are leading causes of non-communicable diseases (NCDs), including cardiovascular disease, respiratory disease, cancer and diabetes.^1 2^ The WHO has determined that reducing the prevalence of behavioural risk factors should be a priority in many societies to reduce the incidence of NCDs and disability-adjusted life-years.^3^ It is therefore important that effective and scalable means of helping individuals to improve their health behaviours are established.

The Public Health Agency of Sweden’s national public health survey from 2020^4^ (n=16 947) reports data on lifestyle behaviours of Swedish citizens aged 16–84. According to the survey, 16% of respondents report hazardous or harmful alcohol consumption, 35% report being insufficiently physically active, 12% report smoking occasionally or daily and 93% report eating less fruit and vegetables than recommended. Additionally, 52% of individuals report being obese or overweight. Unfortunately, with the exception of smoking, the prevalence rates of these behaviours have not decreased markedly over the past 10 years, with some increasing, witnessing of a lost decade for prevention efforts.

For prevention efforts to have an impact on the general population, they need to have extensive reach among those who may benefit. No single setting will be able to achieve this, for example, only 1%–5% of individuals visiting primary healthcare clinics in Sweden are given advice with respect to their lifestyle,^5^ despite many more in need of such advice. Unhealthy lifestyle behaviours also tend to cluster and interact,^6 7^ for example, those who are overweight are more likely to be physically inactive, and excessive alcohol consumption may lead to weight gain. Risks from multiple unhealthy lifestyle behaviours may be multiplicative^8^; thus, it is of value to not only extend the reach of interventions, but to also investigate tools designed to support change of multiple health behaviours.

One way of reaching further into the community with a multiple health behaviour change intervention is to offer digital support tools to those searching online for help. This is especially promising in Sweden, since the internet is used daily by approximately 90% of the population, and the same proportion use smartphones on a regular basis.^9 10^ A recent effectiveness trial of a digital alcohol intervention among online help-seekers in Sweden found evidence of positive effects on alcohol consumption,^11^ but also that only 13.5% of study participants turned off the support, which indicates that receiving support for behaviour change through digital means is an acceptable method for many. Studies evaluating digital interventions addressing multiple health behaviours have also shown promising results.^12–15^ However, the evidence of these types of interventions in more general populations is lacking, as the majority of studies have been conducted among university students, employees within specific fields, or patients with specific health conditions. In addition, behaviour interventions often consist of several components or modules, yet are commonly evaluated as a whole,^16^ leaving a paucity of evidence for the effects of the dismantled components. Increasing our understanding of the effects at the component level, in particular with respect to multiple behaviours, may help move the field of behaviour interventions forward.

### Objectives

This study aims to estimate the effects of the components of a digital intervention on multiple health behaviours (alcohol, physical activity, diet and smoking) among individuals seeking help online. The objectives of the study are to:

Estimate the effects of a digital intervention’s different components on individual health behaviours:Weekly alcohol consumption and number of episodes per month of heavy drinking.Average daily fruit and vegetable consumption.Weekly moderate to vigorous physical activity (MVPA).Four-week point prevalence of smoking.Estimate the degree to which the effects of the components are mediated through perceived importance, confidence and know-how.Detect interactions among health behaviour change, for example, those who stop smoking may also reduce their alcohol consumption, and the degree to which this is moderated by the components of the intervention.

## Methods

A double-blind factorial randomised trial^17^ (six factors with two levels each) will be employed to address the objectives of the study. A Bayesian group sequential design will be employed to periodically make decisions to continue or stop recruitment.^18–20^ This protocol contains relevant items from the Standard Protocol Items: Recommendations for Interventional Trials.^21^ The methods of this trial, including the statistical analysis plan, was preregistered on the Open Science Platform prior to enrolment commenced (https://osf.io/xyj3p/).

### Study setting, recruitment and eligibility

We will recruit individuals seeking information about health and behaviour change by advertising on Google, Bing and Facebook (restricted to Sweden), as well as on websites which focus on lifestyle and behaviour change (eg, livsstilsanalys.se). Individuals exposed to the advert will be advised to sign up to the study by sending a text message with a specific code to a dedicated phone number.

Within 10 min, individuals will receive a text message with a hyperlink that takes them to a web page with informed consent materials. Consent will be given by clicking on a button on the bottom of the page. All individuals giving informed consent will be asked to complete a baseline questionnaire, which will also assess eligibility for the trial (please see online supplemental appendix A). Individuals will be included in the trial if they fulfil at least one of five conditions:

10.1136/bmjopen-2022-061024.supp1Supplementary data

Weekly alcohol consumption: Consumed 10/15 (female/male) or more standard drinks of alcohol the past week. A standard drink of alcohol is in Sweden defined as 12 grams of pure alcohol.Heavy episodic drinking: Consumed 4/5 (female/male) or more standard drinks of alcohol on a single occasion at least once the past month.Fruit and vegetables: Consumed less than 500 g of fruit and vegetables on average per day the past week.MVPA: Spent less than 150 min on MVPA the past week.Smoking: Having smoked at least one cigarette the past week.

Individuals will be explicitly excluded if they do not fulfil any of the criteria or if they are less than 18 years of age. The trial information and intervention will be entirely in Swedish and delivered to participants’ mobile phones, thus not comprehending Swedish well enough to sign up or not having access to a mobile phone will implicitly exclude individuals.

### Interventions

The digital intervention, which is called Coach, consists of six components which users access using their mobile phone, based on an intervention design we have used previously.^22 23^ The intervention is designed around social cognitive theories of behaviour change, with a focus on modifying environment, intention and skills.^24 25^ The intervention’s components are intended to be used as a toolbox, allowing users to choose which parts of the intervention to interact with and tailor the support to their needs. Participants eligible for the trial will be allocated to one of 64 factorial conditions, each condition representing a unique combination of the six components—which are either present or absent (2^6^=64 conditions). The intervention materials can be accessed at participants’ discretion over a 4-month period, and each Sunday afternoon participants will receive a text message with a link and a reminder to access the intervention materials. A summary of the components is presented in table 1, and a detailed description of the six components is available in online supplemental appendix B.

10.1136/bmjopen-2022-061024.supp2Supplementary data

**Table 1 T1:** Brief description of the six components of the coach intervention

Screening and feedback	Present/absent
Every Sunday afternoon, participants will receive a text message with a hyperlink which takes them to a questionnaire regarding their current health behaviours. Once complete, feedback on their current behaviour is given in relation to national guidelines. Thereafter users are given access to the rest of the components (depending on allocation).	When absent participants will not be shown the questionnaire but instead only national guidelines without personal feedback.
**Goalsetting and planning**	
This component let participants set a goal for their future behaviour and plan for what to do when they struggle and succeed. Participants can also accept challenges for the coming week, for example, to walk for 15 min each day, or to not drink any alcohol this week. Self-composed challenges are also available. Reminders are sent via texts to participants about their goals and challenges throughout the week.	When absent, this component will not be visible.
**Motivation**	
This component contains information and tools to increase participants’ motivation for change. This includes information on negative health consequences, costs induced from certain behaviours and reflective tasks. If participants choose, they can also activate motivational text messages which are sent to them throughout the week.	When absent, this component will not be visible, and text messages will not be available.
**Skills and know-how**	
Concrete tips on how to initiate and maintain change in everyday life is offered in this component. This includes giving participants strategies they can use to say no to alcoholic beverages at parties, how to increase the nutritional value of their breakfast, etc. If participants choose, they can also activate text messages with tips sent to them throughout the week.	When absent, this component will not be visible, and text messages will not be available.
**Mindfulness**	
This component aims to increase users’ awareness of their own lived experience and strengthen their capacity for non-reactive, compassionate and less stressful way of being in the world. Mindfulness exercises are offered to participants, including guided meditations.	When absent, this component will not be visible, and guided meditations not available.
**Self-composed text messages**	
Participants are given the opportunity to compose messages and have them sent to themselves throughout the week (on days and times of their own choosing). A participant may for instance write a message to themselves reminding them to eat two fruits each day, to not drink anything on Wednesdays, or to go for a walk with a friend.	When absent, this component will not be visible.

### Outcomes

#### Measures

Outcomes are listed here and subsequently explained. All questionnaires (baseline, 1-month, 2-month and 4-month follow-up) used in the trial can be found in online supplemental appendix A.

##### Primary outcome measures

Alcohol: Weekly alcohol consumption; monthly frequency of heavy episodic drinking.Diet: Average daily consumption of fruit and vegetables.Physical activity: Weekly MVPA.Smoking: Four-week point prevalence of smoking abstinence.

##### Secondary outcome measures

Perceived stress.Weekly consumption of sugary drinks.Weekly consumption of candy and snacks.Body mass index (BMI)Body mass index (BMI).Weekly number of cigarettes smoked.Quality of life (QoL).

##### Mediation measures

Importance of change.Confidence in one’s ability to change.Knowledge of how to change.

### Primary and secondary outcomes

Weekly alcohol consumption will be assessed by asking participants the number of standard drinks of alcohol they consumed last week (short-term recall method^26^). Frequency of heavy episodic drinking will be assessed by asking participants how many times they have consumed 4/5 (female/male) or more standard drinks of alcohol on one occasion the past month. These two outcomes are both part of the proposed core outcome set for brief alcohol interventions,^27–29^ and represent different risk behaviours which are sometimes found in the same individual and sometimes not. For instance, one may have a high weekly alcohol consumption, and thereby be at risk for negative health consequences, without consuming 4/5 or more drinks on the same occasion. Similarly, having one episode of heavy episodic drinking increases the risk of short-term consequences (such as injury) and long-term health consequences, but does not fulfil the criteria for total weekly consumption.

Diet and physical activity will be measured using a questionnaire based on the previously published questionnaire by the National Board of Health and Welfare in Sweden,^7^ and was further modified to also include portion sizes. The consumption of fruit and vegetables will be measured using two questions concerning the number of portions (100 g) of fruit and vegetables (respectively) the participants ate on average per day during the past week. Sugary drinks consumption will be measured by a question regarding the number of units (33 cl) of sugary drinks participants consumed the past week, and candy and snacks will be measured using a single question regarding number of servings consumed last week. MVPA will be estimated by summing responses to two questions regarding the number of minutes spent on moderate and vigorous physical activity, respectively, during the past week.

BMI will be measured by asking participants to report their weight and height.

Four-week point prevalence of smoking abstinence (no cigarettes the past 4 weeks) will be asked as a binary question. This is a suggested measure by the Society of Research on Nicotine and Tobacco.^30^ Participants who have smoked any cigarette the past 4 weeks will be asked for the number of cigarettes smoked the past week.

QoL will be measured using PROMIS Global 10,^31^ both to estimate the degree to which intervention components effect QoL but also for health economic evaluations. Perceived stress will be assessed using the short form Perceived Stress Scale-4.^32^

#### Mediation measures

Participants will be asked to report on confidence, importance and know-how, which are three psychosocial factors believed to be important markers of behaviour change.^24 25 33–35^ To reduce participant burden, we will use single face-valid items, acknowledging the limitation of such measures.

### Participant timeline and follow-ups

A trial participant timeline is presented in figure 1. Intervention components (depending on allocation) will be made available to participants all at once and stay available to participants at their own discretion throughout the 4-month period (with weekly reminders). There are three follow-up stages: 1-month, 2-month and 4-month postrandomisation. All follow-ups will be initiated by sending text messages to participants with hyperlinks to questionnaires. The following additional attempts will be made to collect data:

A total of two text reminders will be sent 2 days apart to those who have not responded.If there is no response to the mediator questions at the 1-month follow-up, then the questions will be sent in a text message and participants are asked to respond directly with a text.If there is no response to the 2-month and 4-month follow-ups, then we will call participants to collect responses for the primary outcome measures only. A maximum of five call attempts will be made.

**Figure 1 F1:**
[figure not shown]
SPIRIT figure showing participant timeline throughout the study. SPIRIT, Standard Protocol Items: Recommendations for Interventional Trials.

### Assignment of interventions

Randomisation will be fully automated and computerised. Block randomisation will be used to allocate participants to the 64 conditions (random block sizes of 64 and 128). Neither research personnel nor participants will be able to influence allocation.

Research personnel will be blind to allocation throughout the trial. All participants will have access to the intervention, although with different components, and they will not be made aware of the other available conditions and will therefore be blind to allocation.

### Patient and participant involvement statement

Outcome measures used in the trial are informed by national guidelines in Sweden, as well as those set by the WHO. Also, the Swedish National Board of Health and Welfare^7^ have reported that research regarding multiple health behaviour change interventions is lacking. No patients or participants were involved in the planning of this trial or design of the intervention; however, both have been informed by our previous research involving individuals looking for help to change health related behaviours.

## Analysis

All analyses will be done keeping all participants in the groups to which they were randomised. Analyses will be done using both available data and imputation. Imputation will be done using multiple imputation with chained equations.^36^ The implicit missing at random (MAR) assumption underlying this approach will be investigated by two attrition analyses: (1) if data are missing systematically then it may be the case that early responders (answering without reminders) differ from non-responders (requiring several attempts), and in extension that late responders are more alike non-responders. Therefore, one attrition analysis will regress primary outcomes against number of attempts to collect follow-up before a response was recorded; (2) we will further explore the MAR assumption by investigating if responders and non-responders are different with respect to baseline characteristics.

Groups will be contrasted using multilevel regression models with covariates for group by component interactions and participant level adaptive intercepts. Models of longitudinal data (primary outcomes and perceived stress) will include group by time by component interactions. We will explore pairwise interactions among components. Bayesian inference will be used to estimate the parameters of the models^37–39^ (see Sample Size for priors). For each coefficient of interest, we will report the marginal posterior probability of effect, and the median will be used as a point estimate of the magnitude of the effect. We will also report on 50% and 95% compatibility intervals.

### Models

#### Primary and secondary outcomes

Analyses of primary outcomes will be conducted among those fulfilling the respective criteria for inclusion at baseline, for example, weekly alcohol consumption will be analysed among those who reported having consumed 10/15 (female/male) or more units of alcohol the past week. BMI, sugary drinks, candy/snacks, QoL and perceived stress will be analysed among all participants, and number of cigarettes smoked weekly among baseline smokers.

Weekly alcohol consumption, frequency of heavy episodic drinking per month, weekly intake of candy and snacks, number of sugary drinks per week and cigarettes smoked per week are all count variables that are likely skewed and over dispersed. Therefore, these outcomes will be analysed using negative binomial regression. If found not to be over dispersed, we will consider using normal regression (possibly log transformed). Average intake of fruit and vegetables per day, MVPA minutes per week, BMI, QoL and perceived stress will be analysed using normal regression (possibly log transformed). Point prevalence of smoking abstinence will be analysed using logistic regression.

All models will be adjusted for age, sex and mediators (importance, confidence and know-how) at baseline. Primary outcomes and perceived stress will be adjusted for their respective baseline values, except for smoking prevalence which will be adjusted by the weekly number of cigarettes smoked at baseline. BMI, sugary drinks and candy/snacks will be adjusted for baseline MVPA minutes per week and average intake of fruit and vegetables per day. Number of cigarettes smoked last week will be adjusted by its baseline value. QoL will be adjusted for perceived stress at baseline.

In addition to pairwise interactions between components, effect modification will be explored in all models to assess if any of the baseline characteristics moderate the effects of the components of the intervention.

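### The weekly-alcohol model's only baseline drinking covariate is the past-week count that selects its participants; leaving out the past-month heavy-drinking count gives up a modest, assumption-dependent amount of precision

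*Protocol article*

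**What the plan says.** The subsection on primary and secondary outcomes under Models (protocol article, Analysis) restricts the analysis set by outcome: "weekly alcohol consumption will be analysed among those who reported having consumed 10/15 (female/male) or more units of alcohol the past week". The same subsection names the covariates: "All models will be adjusted for age, sex and mediators (importance, confidence and know-how) at baseline", and then "Primary outcomes and perceived stress will be adjusted for their respective baseline values", with smoking abstinence as the exception.

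The subsection of the same name under Outcomes defines the two alcohol measures. Weekly consumption comes from "asking participants the number of standard drinks of alcohol they consumed last week". Heavy episodic drinking is "how many times they have consumed 4/5 (female/male) or more standard drinks of alcohol on one occasion the past month". The authors say that the two "represent different risk behaviours which are sometimes found in the same individual and sometimes not".

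Both measures are eligibility conditions, and under Study setting, recruitment and eligibility "All individuals giving informed consent will be asked to complete a baseline questionnaire, which will also assess eligibility for the trial". Heavy episodic drinking is also a primary outcome adjusted for its own baseline value, so a baseline count must exist. The questionnaire itself is in an appendix that is not shown.

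**The concern.** The baseline drinking covariate in this model has two weaknesses as a predictor. It was cut at the selection threshold, which narrows its range. Some participants passed the threshold because that one week was heavier than usual for them, so part of its remaining spread is week-to-week noise. The heavy-drinking count covers about four times as long and was not the variable cut. It should carry information about usual drinking that the past-week count lacks, yet it is not in the model.

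Elsewhere the plan does use related baseline measures. Smoking abstinence is adjusted for cigarettes per week; BMI, sugary drinks and candy/snacks for physical activity and fruit and vegetables; and quality of life for stress. The two linked alcohol measures are not used this way.

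At stake is the width of the posterior for six component effects, at two follow-ups each, on a primary outcome analysed in a subgroup of the trial.

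**Working it through.** **Inputs from the protocol article**

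| Item | Value | Where |
|---|---|---|
| Analysis set | past-week count at least 10/15 (female/male) | Models |
| Own baseline covariate | the same past-week count | Models; Outcomes |
| Other covariates | age, sex, baseline importance, confidence, know-how | Models |
| Omitted candidate | past-month count of heavy episodes | Outcomes; eligibility |
| Allocation per component | 1:1 | Sample size |
| Correlation of the two measures, dispersion, subgroup size | not given | – |

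**Step 1: the plan's own figure.** The article gives no precision figure for this model. Its only size figure is 1500–2500 participants in total. For a standardised outcome the standard error is 2/√N, so 1.96 × 2/√N = 0.10 gives N = 4 × 19.6² = 1537, near the lower end. The full range cannot be reproduced because its simulation inputs are not stated. The point does not depend on it.

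**Step 2: formula.** Write y for log follow-up drinking, w for the log past-week count and h for log(1 + heavy episodes). With 1:1 randomisation the variance of a component effect is about 4σ²/n, where σ² is the residual variance. Adding h multiplies σ² by 1 − ρ², with

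ρ = (r_yh − r_yw·r_wh) / √[(1 − r_yw²)(1 − r_wh²)].

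Two examples with assumed correlations:

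- r_yw = 0.4, r_yh = 0.3, r_wh = 0.4: ρ = (0.30 − 0.16)/0.84 = 0.167, so the variance falls by 2.8%.
- r_yw = 0.3, r_yh = 0.4, r_wh = 0.2: ρ = (0.40 − 0.06)/√(0.91 × 0.96) = 0.364, so the variance falls by 13.2%.

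Over a grid of r_yw 0.3–0.6, r_yh 0.2–0.4 and r_wh 0.2–0.6 the fall is 0% to 13%.

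**Step 3: simulation with the 10/15 selection and a chosen correlation.** Assumptions: median usual intake 9 (women) and 13 (men) drinks a week, 40% men, between-person log-SD 0.6 or 0.8, week-to-week log-SD 0.3 or 0.5, personal change by follow-up with log-SD 0.3 or 0.6, and four values for the latent correlation of heavy episodes with usual intake. Log follow-up count was regressed on log past-week count and sex, then on those plus log(1 + heavy episodes). This gives 32 scenarios.

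| Latent correlation | Variance cut | Standard-error cut |
|---|---|---|
| 0.3 | 0.2–0.9% | 0.1–0.4% |
| 0.5 | 0.7–2.4% | 0.3–1.2% |
| 0.7 | 1.9–5.5% | 0.9–2.8% |
| 0.85 | 3.3–9.6% | 1.7–4.9% |

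A cut of 4% or more appears in 10 of 32 scenarios, all at 0.7 or 0.85. After selection the past-week count correlated 0.32–0.62 with follow-up drinking.

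**Step 4: simulation from drinking occasions.** Here both measures are generated from the same occasions and drinks per occasion, so their correlation follows from the process.

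- Sixteen settings, with the own baseline already log-transformed, gave a variance cut of 2–12% for the component log rate ratio. On the standard-error scale this is 1 − √0.98 = 1.0% to 1 − √0.88 = 6.2%. It is equivalent to 1/0.98 − 1 = 2% to 1/0.88 − 1 = 14% more analysed drinkers.
- In a separate set of 16 such settings the heavy-episode count correlated 0.66–0.82 with usual intake before selection. After selection it tracked usual intake better than the selecting count did in every setting (0.58–0.76 against 0.48–0.67). The variance cut was 3–11%.
- Seven further settings gave about 1–16%. The four with recall error in the heavy-episode count gave about 1–6%.

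**The case against.** Adjusting an outcome for its own baseline, with age, sex and other baseline items, is standard and valid in a randomised comparison. An extra covariate is an option, and a reviewer could propose many. The occasion-based simulations build in a strong link between the two measures, whereas the article stresses that the two risks need not occur in the same person. All the simulations are also simpler than the planned Bayesian multilevel model with two follow-ups, and they omit age and the psychosocial items, which could lower the gain further. The past month includes the selecting week, so the heavy-drinking count is not wholly free of the same inflation. And the plan was preregistered before enrolment, so a change to a primary model is a departure from it.

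All of this stands as a limit on the size of the point. It does not remove the point: the covariates are fixed outcome by outcome in the article, the omitted item is already collected, and in large samples adding it helps or is neutral.

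Several stronger readings are tempting and are not supported:

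- *The model adjusts for nothing but the past-week count.* It also has age, sex and three psychosocial items.
- *Selection on the baseline count biases the component effects.* Regression to the mean affects both levels of each randomised component alike.
- *All component effects in the trial lose precision.* Only the six on weekly alcohol are concerned.
- *Recruitment will run longer.* Weekly alcohol supplies 12 of the 60 stopping cells (6 components × 2 times, out of 6 × 2 × 5 outcomes), but the slowest cell governs, the criteria are described as targets, and nothing shows that weekly alcohol is the slowest.
- *Baseline counts enter the negative binomial models untransformed.* The article does not say, and may leave this to the analysis plan.

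**Conclusion.** The point holds as a modest missed efficiency. It is neither an error nor a contradiction. The direction is secure, because the covariate is measured before randomisation and the components are randomised; under the log link the rate ratio keeps its meaning when the covariate is added. The size is not secure. It is about 2–12% of the variance (1–6% of the standard error) if both measures arise from the same drinking occasions as assumed, and near 0–2% if they are only weakly or moderately correlated. No figure in the documents decides between these.

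**What to change.** Add to the covariate paragraph under Models: *Weekly alcohol consumption will also be adjusted for baseline monthly frequency of heavy episodic drinking, entered as log(1 + count).* Use the same covariate in the interim models, so that the stopping criteria and the final analysis rest on one specification. Because the plan was preregistered, recruitment has begun and interim analyses are planned for every 50 completers, record this as a dated change and state that it was decided without reference to component effects. If the registered analysis plan already contains this covariate, the article only needs to be brought into line with it.

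The cost is one sentence, one extra coefficient and an entry in the change record. No new data are needed and no participants are lost.
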